## Abstract

**Background:**

Ageing entails changes in complex cognitive functions that lead to a decrease in autonomy and quality of life. Everyday cognition is the ability to solve cognitively complex problems in the everyday world, enabling instrumental activities of life. Benefits have been found in studies using everyday cognition-based assessment and intervention, as the results predict improvements in everyday performance, not just in specific cognitive functions. A study protocol is presented based on assessment and training in everyday cognition versus traditional cognitive stimulation for the improvement of functionality, emotional state, frailty and cognitive function.

**Methods:**

A parallel randomised controlled clinical trial with two arms will be conducted. It will be carried out by the University of Salamanca (Spain) in eleven centres and associations for the elderly of the City Council of Salamanca. People aged 60 years or older without cognitive impairment will be recruited. Participants will be randomly distributed into two groups: the experimental group will undergo a training programme in everyday cognition and the control group a programme of traditional cognitive stimulation, completing 25 sessions over 7 months. All participants will be assessed at the beginning and at the end of the intervention, where socio-demographic data and the following scales will be collected: The Medical Outcomes Study (MOS), Questionnaire ARMS-e, Everyday Cognition Test (PECC), Scale Yesavage, Test Montreal Cognitive Assessment (MoCA), The Functional Independence Measure (FIM), Fragility Index and Lawton y Brody Scale.

**Discussion:**

The present study aims to improve conventional clinical practice on cognitive function training by proposing a specific assessment and intervention of everyday cognition based on the importance of actual cognitive functioning during the resolution of complex tasks of daily life, giving priority to the improvement of autonomy.

**Trial registration:**

ClinicalTrials.gov; ID: NCT05688163. Registered on: January 18, 2023.

## Background

For the first time in history, most people worldwide can live to be over 60 years old [1]. This increase in life expectancy, coupled with a declining birth rate, explains why the population has been ageing significantly in recent years. And although ageing is associated with physical, cognitive, psychological and sensory changes [2], diversity in old age is immense. Many international bodies have advocated an approach focused on promoting health far beyond the absence of disease. Of particular note is the approach promoted by the WHO since the 90’s, which defines healthy ageing as the process of optimising opportunities for health, participation and security in order to improve quality of life [3,4].

In older adults, one of the causes of decreased functionality is the loss in terms of cognitive performance [5]. Cognition is a complex and dynamic system of interconnected components that allows us to process, organise and use information in order to be functional in our environment, and for this the different cognitive components or processes must be coordinated [6]. Cognitive ageing is characterised by a decline in complex cognitive functions such as attention, working memory, processing speed, executive control and episodic memory [7]. However, other functions are maintained, such as implicit memory, language and acquired knowledge [8]. People in their everyday functioning need these cognitive functions to solve problems or situations, which is where the term "everyday cognition" comes in. This concept establishes the basis for the present study protocol and is defined as the ability of people to solve cognitively complex problems in the real or everyday world [9], allowing them to carry out instrumental activities of daily life in a functional manner. Another subdomain that is present in the resolution of these activities is the psychological or emotional problems that older adults may face in their daily lives, such as depression [10,11].

Occupational therapy is one of the healthcare disciplines that use neurocognitive approaches to maintain or improve functionality in the elderly population [12,13]. Various approaches exist within this discipline to achieve this objective. The most commonly used approach is traditional cognitive stimulation, which involves group activities targeting specific cognitive functions, such as attention or memory. However, this poses a challenge in terms of transferring and generalising the results to everyday functioning. In response, interventions based on everyday cognition are being implemented, specifically, training in complex everyday problems such as managing finances, medication, or transportation, to improve or maintain autonomy in daily life.

There have been studies [14,15] that have established important findings regarding the use of assessments of everyday cognition versus the use of traditional cognitive performance assessment tools. It is considered that the former may be more effective in preventing the evolution of functional deficits in neurodegenerative diseases; being predictors of the initial stage of the disease and its development.

With respect to the intervention in everyday cognition, we should point out that it has limited scientific evidence and scope, due to the few projects that have been based on this type of intervention model to date. The use of this method could solve the problems of conventional intervention to generalize the results in the daily performance of older adults, since its effectiveness is shown in improvements of specific cognitive functions, without being able to be transferred to the real life of older adults.

Based on the above, we propose as an intervention a training programme in everyday cognition, as opposed to traditional cognitive stimulation programmes. It would involve carrying out an assessment and an intervention focused on the training of basic cognitive functions during the performance of activities that the older adult carries out on a daily basis with materials that are the same or similar to those of real life; as opposed to other traditional programmes that focus on training isolated cognitive functions, without taking into account whether there is the possibility that this type of intervention will subsequently produce benefits in the daily life of the trained subject. The findings will provide important insights for the development of an intervention model that we believe may be more effective in maintaining cognition and functioning in older adults.

### Aim

In line with the above, the main objective of this study is to test our hypothesis that intervention through a specific training programme in everyday cognition will increase the beneficial effects of traditional cognitive stimulation programmes as an intervention on cognitive function, emotional state, frailty and functionality in older adults without cognitive impairment. The objectives are to compare the effects produced by the application of a specific training programme in everyday cognition versus the isolated intervention on cognition by means of a traditional cognitive stimulation programme in older adults without cognitive impairment.

## Material and methods

### Design and setting of the study

An experimental, prospective, randomised, parallel-controlled, clinical trial will be carried out with two arms of fixed allocation with an experimental group and a control group. It will be conducted for one year at the University of Salamanca (Spain) in eleven municipal centres and associations for the elderly belonging to the Salamanca City Council. Participants belonging to the occupational therapy programmes of the Geriatric Revitalisation Project organised by the University of Salamanca, aged 60 years or older without cognitive impairment at the time of inclusion, will be recruited.

### Sample/Participants

#### Participants

The study population will be composed of people aged 60 years or older without cognitive impairment who voluntarily agree to participate in the Occupational Therapy programme of the Geriatric Revitalisation project organised by the University of Salamanca in collaboration with the Salamanca City Council (Spain), within the framework of the Research in Active Ageing agreement. Regarding the location, the study will be carried out in eleven municipal centres and associations for the elderly belonging to the Salamanca City Council, Spain. The researchers of the University of Salamanca will invite older adults to participate in the study by explaining the details of the clinical trial and they can be included once they have given their verbal and written consent and meet the following selection guidelines: (A) Inclusion criteria: Being 60 years of age or older, voluntarily signing the informed consent form authorising participation and completing the initial assessment. (B) Exclusion criteria: Not having knowledge of reading and writing or significant deficits in language comprehension, being institutionalised, to have a clinical diagnosis of a neurocognitive disorder included in the DSM-V at the time of the initial assessment and participating in another cognitive stimulation programme. (C) Withdrawal criteria: Dropping out of the programme.

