#### Sample size

The sample size has been estimated using Epidat 4.2. A one-sided approach has been assumed with a confidence level of 95% and a statistical power of 80%. It has been decided to take equal sizes in the two groups (i.e. R = n2/n1) and the Yates correction will not be applied. The sample size calculation was based on the results of a similar RCT, specifically the study conducted by Fernández et al. in 2018 [16] which compared the outcomes of a traditional cognitive stimulation intervention versus an intervention based on everyday cognition. The primary variable chosen in both studies was everyday cognition. The study found that the experimental group (those who received everyday cognition training) demonstrated an improvement of 2.57 points in the primary variable, while the control group (those who received traditional cognitive stimulation) only demonstrated an improvement of 0.39 points. With an expected population loss of 20%, the final sample size was n = 99 participants, with 50 in the experimental group and 49 in the control group.

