### Procedures and data collection

#### Evaluations and study plan

Participants will be assessed at two points during the study: the baseline assessment at the beginning of the study and the final assessment after the end of the intervention. The baseline assessment will take place after recruitment and before randomisation and allocation of subjects to the corresponding group. This initial assessment includes the recording of the independent variables and the primary outcome variables to be studied; the intervening variables will be recorded and several objective assessment tests will be used. Then, after randomisation, the intervention for each group will be carried out. Then, another assessment will be carried out, considered the final assessment, where participants will be asked to complete the same objective tests as in the initial assessment. The results will be notified by means of an individual and personal report to those persons who expressed the wish at the beginning to receive the information corresponding to the results and evolution. All evaluations will be carried out by research staff, previously trained and instructed in this process. This process can be seen in more detail in Fig 2 which includes a flow chart of the study methodology.

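### Dropping out of the sessions is defined as withdrawal from the study, so followed as written the trial compares only those who stayed in their programme

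*Protocol article*

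**What the plan says.** All references are to the protocol article.

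- **Participants.** After the inclusion and exclusion criteria comes a single rule for leaving: "C) Withdrawal criteria: Dropping out of the programme". No other ground for withdrawal is given.
- **Evaluations and study plan.** The order is baseline assessment, randomisation, intervention, then one further assessment, "considered the final assessment, where participants will be asked to complete the same objective tests as in the initial assessment".
- **Interventions.** Both programmes have weekly sessions for 7 months, 25 in all. Number, length and format are the same. The tasks differ: everyday problems with lifelike materials in one arm, paper exercises on separate cognitive functions in the other.
- **Data analysis.** The dependent variable is the difference between the initial and the post-intervention result.
- **Sample size.** "With an expected population loss of 20%, the final sample size was n = 99 participants". The arms are to have 50 people (experimental) and 49 (control). The 20% is not split by cause or by arm.
- **Abstract, Methods.** All participants are to be assessed at the start and at the end of the intervention.

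**The concern.** Stopping a training programme and leaving a trial are different events. The first ends exposure to the sessions; the second ends data collection. The rule in the Participants section merges them.

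The merger acts after allocation, over seven months of material that differs by arm, so who leaves and why can depend on the arm. A leaver who is not assessed at the end has no change score. The two sets of people compared are then no longer the two sets that were randomised, and the result describes people who kept attending rather than the consequence of offering one programme instead of the other.

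A later analysis plan can model a missing final score but cannot observe it. That is why the wording of the rule matters now and cannot simply be left to the analysis stage.

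**Working it through.** **1. How many people could be affected.**

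Inputs from Sample size: total 99 (50 + 49) and expected loss 20%.

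- Expected losses: 99 × 0.20 = 19.8, about 20.
- Expected remaining: 99 × 0.80 = 79.2, about 79.
- Check on the stated total: 79 / (1 - 0.20) = 98.75, which rounds up to 99. The total is consistent with inflating 79 evaluable people for 20% loss. It also fits 82 × 1.2 = 98.4, rounded up to 99, so the route is not certain. No standard deviation is given, so 99 cannot be rebuilt from the effect size alone.

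**2. The planned effect.**

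The section says that the experimental group of an earlier trial "demonstrated an improvement of 2.57 points in the primary variable" and gives 0.39 for its control group. Difference: 2.57 - 0.39 = 2.18 points.

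**3. What a stayers-only comparison does.**

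Let d be the share of an arm that leaves, and g the number of points by which leavers change less than stayers. The mean change in the whole arm is then the stayers' mean minus d × g. With E for experimental and C for control:

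bias of the stayers-only difference = d_E × g_E - d_C × g_C

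A positive value favours the experimental arm. The documents give neither d by arm nor g, so every value below is an assumption. Each loss pattern averages 20% over the two arms.

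| Loss E / C | g_E = g_C = 1.00 | g_E = g_C = 2.18 | g_E = 2.18, g_C = 0 | g_E = 2.57, g_C = 0.39 |
|---|---|---|---|---|
| 20% / 20% | 0 | 0 | +0.44 | +0.44 |
| 25% / 15% | +0.10 | +0.22 | +0.55 | +0.58 |
| 30% / 10% | +0.20 | +0.44 | +0.65 | +0.73 |
| 15% / 25% | -0.10 | -0.22 | +0.33 | +0.29 |

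Worked ends of the range:

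- Highest: 0.30 × 2.57 - 0.10 × 0.39 = 0.771 - 0.039 = +0.73, and 0.732 / 2.18 = 34%.
- Lowest: 0.15 × 2.18 - 0.25 × 2.18 = 0.327 - 0.545 = -0.22, which is -10% of 2.18.
- Balanced loss with equal g: 0.

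The last column is the case in which stayers change by the planned amounts and leavers do not change at all.

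**4. Whether the sample-size allowance covers this.**

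Dividing by 1 - 0.20 restores the number of people analysed. It does not enter the bias formula, where only d and g appear. The allowance protects power and leaves selective loss untouched.

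**The case against.** The strongest counter-argument is textual. The Abstract says that all participants are assessed at both times, and the passage on the final assessment does not limit it to people who finished the sessions. On that reading leavers are still tested and nothing is lost. This stands as an ambiguity but not as an answer: someone withdrawn under the rule may no longer count as a participant, and nothing says that leavers are recalled.

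Second, this is a condensed article. The analysis population and the handling of missing data may be in a fuller document, and the flow chart is not shown. That is fair, and silence on those matters is not held against the plan. The withdrawal rule, however, is stated text.

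Third, the design limits differential drop-out: the two programmes match in number, length and format of sessions, rooms are similar, and participants are not told their group. This makes imbalance less likely. It does not rule it out, because participants experience the content.

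Three stronger readings are tempting and are not supported:

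- *That the rule causes the 20% loss.* The figure has no stated cause and no link to the rule; illness, moving away or refusal would count too.
- *That the protocol excludes leavers from the analysis.* It does not say so. That follows only from combining the rule with one final assessment and a change score.
- *That the result will overstate the effect by a quarter,* from 2.18 / (2.18 × 0.80) = 1.25. This takes 2.18 to be an effect in completers, which the article does not say, and assumes that even someone who stops late gains no differential benefit.

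Nor should much be made of recovered power. Allocation is by eleven groups, so extra members of the same groups add less than their number suggests.

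**Conclusion.** The point holds as a defect in one stated rule that should be corrected. As written, stopping the sessions ends participation in the study, and with one final assessment and a change-score outcome that removes the person from the comparison. Up to about 20 of 99 people could be affected, if all of the planned loss were of this kind.

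The direction and size of any bias cannot be known in advance. Under the assumed patterns it lies between about -0.2 and +0.7 points against a planned 2.18, and it vanishes when loss and prognosis are balanced. The case rests on keeping the randomised comparison intact, not on a predicted bias in favour of the experimental arm.

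**What to change.** Reword the withdrawal criterion so that stopping the programme ends the sessions only. The participant remains in the study and is still invited to the final assessment unless consent is withdrawn. Bring the Participants section and the Abstract into line on this. Analyse everyone assessed in the arm allocated to their group, and report a completer analysis as supportive. Record the number of leavers and their reasons by arm.

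The cost is one protocol sentence, reported to the ethics committee as the article already provides for, plus one contact and one assessment visit for each person who stops, at most about 20. The external assessors are already planned. The visit is not trivial: the stated administration times for the everyday cognition test, the MoCA, the depression scale and the Lawton and Brody scale add to 35 + 10 + 5 + 4 = 54 minutes, and the functional independence and frailty measures have no stated time. Some leavers will decline or be unreachable, so the change reduces the loss rather than removing it. The required sample size does not change.

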#### Randomisation

Participants voluntarily enroll in one of the eleven groups that belong to different senior centers to receive one of two types of cognitive intervention. In order to ensure the greatest fairness among the different groups, a maximum of 15 and a minimum of 5 participants per group were established. Following recruitment, randomization will be carried out through simple allocation of each group belonging to each senior group by using the Epidat 4.2 program. The eleven intervention groups will be allocated to either the experimental or control group as detailed in Fig 1 of the SPIRIT 2013 registration, interventions and assessments program.

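### Simple allocation of eleven unequal groups does not secure the equal arms the sample size assumes: an 8:3 split of groups or worse has a 23% chance, at an avoidable cost in precision

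*Protocol article*

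**What the plan says.** All references are to the Protocol article.

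- **Randomisation.** Participants enrol themselves in one of eleven groups at senior centres, and "a maximum of 15 and a minimum of 5 participants per group were established". After recruitment, "randomization will be carried out through simple allocation of each group belonging to each senior group by using the Epidat 4.2 program". The section adds that "The eleven intervention groups will be allocated to either the experimental or control group" and points to Fig 1, which is not shown in the text at hand. The caption describes that figure as a schedule of enrolment, interventions and assessments. The section states no blocking, stratification, minimisation or other constraint.
- **Sample size.** "It has been decided to take equal sizes in the two groups", and after allowance for 20% loss "the final sample size was n = 99 participants, with 50 in the experimental group and 49 in the control group".
- **Evaluations and study plan.** "The baseline assessment will take place after recruitment and before randomisation".
- **Design and setting of the study.** The two arms are described as having a fixed allocation. No number of groups per arm is given.
- **Data analysis.** The planned ANCOVA lists age, gender, education level, marital status and occupation as covariates. The sentence does not make clear whether the baseline value of the outcome is one of them.

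**The concern.** The sample size rests on equal arms, but the stated method controls neither the number of groups per arm nor the number of people. With many individuals randomised one by one, simple allocation comes close to balance. With eleven units of unequal size it often does not.

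Two things are at stake. The first is precision, since a lopsided split widens the confidence interval for the treatment difference. The second is chance imbalance. People choose their own centre, so groups may differ in baseline PECC, and a draw of eleven units protects little against such differences falling unevenly between the arms. Group sizes and baseline scores already exist when the draw is made, so nothing in the plan's timing prevents a restricted draw.

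**Working it through.** **1. The plan's own figure.** The 99 participants cannot be reproduced because no standard deviation is given. The difference is 2.57 − 0.39 = 2.18 points, with a one-sided 5% level and 80% power. Since 99 × 0.8 ≈ 79, about 40 evaluable participants per arm are implied. Solving for the SD: 2.18 / [(1.645 + 0.842) × √(2/40)] ≈ 3.92. This SD is inferred and is used only in step 4.

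**2. Groups per arm.** The input is eleven groups, each assumed to be an independent 1:1 draw. The number in one arm is then Binomial(11, 0.5), and the split 11−k : k has probability 2 × C(11, k) / 2048. With equal-sized groups, information relative to 6:5 is k(11−k)/30.

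| Split | Probability | Relative information |
|---|---|---|
| 6:5 | 924/2048 = 45.1% | 1.00 |
| 7:4 | 660/2048 = 32.2% | 28/30 = 0.93 |
| 8:3 | 330/2048 = 16.1% | 24/30 = 0.80 |
| 9:2 | 110/2048 = 5.4% | 18/30 = 0.60 |
| 10:1 | 22/2048 = 1.1% | 10/30 = 0.33 |
| 11:0 | 2/2048 = 0.1% | 0 |

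- 7:4 or better: 1584/2048 = 77%.
- 8:3 or worse: 464/2048 = 22.7%.
- 9:2 or worse: 134/2048 = 6.5%.
- Average relative information: E[k(11−k)]/30 = (11 × 10/4)/30 = 27.5/30 = 0.917.

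These probabilities need no SD, intraclass correlation (ICC) or group-size distribution.

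**3. Participants per arm.** Group sizes are not given, so they were assumed uniform on 5 to 15 with the total held at 99, and the draw was simulated.

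| Outcome | Simple allocation | 6:5 fixed |
|---|---|---|
| One arm under 40% of participants | about 54% | about 15% |
| One arm under one third | about 29–30% | about 1% |
| Both arms within 45–54 participants | about 24% | about 50% |

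At the other extreme, with nine people in every group (99/11), simple allocation still puts one arm under 40% in about 55% of draws. A fixed 6:5 always gives 54:45.

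**4. Power.** Assumptions: SD 3.92, 9 × 0.8 = 7.2 evaluable people per group, normal approximation, one-sided 5%. The design effect is DE = 1 + (7.2 − 1) × ICC. The formulas are SE = 3.92 × √{DE × [1/(7.2k) + 1/(7.2(11−k))]} and power = Φ(2.18/SE − 1.645).

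For 8:3 with ICC 0: SE = 3.92 × √(1/21.6 + 1/57.6) ≈ 0.99, so power = Φ(2.20 − 1.645) ≈ 71%.

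| Split | ICC 0 | ICC 0.05 (assumed) |
|---|---|---|
| 6:5 | 79% | 69% |
| 7:4 | 77% | 67% |
| 8:3 | 71% | 61% |
| 9:2 | 60% | 51% |
| Average over simple allocation | 76% | 66% |

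**5. Room for a restricted draw.** There are C(11, 5) = 462 ways to choose the five-group arm. Under the assumed sizes, requiring 47–52 participants in each arm leaves a median of 144 (5th to 95th percentile 124 to 154). A further condition on baseline PECC would reduce this number. By how much cannot be said without the data.

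**The case against.** **The split may have been preset.** The design section calls the allocation fixed, the Randomisation section defers to a figure that is not shown, and equal arms are assumed. Simple allocation could therefore mean an unstratified draw of a set number of groups. This is a fair point and it lowers certainty. No number of groups per arm is stated, though, and the figure's caption describes a schedule. If 6:5 was preset, the group-count table no longer applies. What remains is that about 15% of draws leave an arm under 40% of participants, and that baseline balance is not controlled.

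**The usual cost is modest.** This stands. In 77% of draws the split is 7:4 or better, and 7:4 loses only two to three points of power. The material loss lies in the 23% tail.

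**Missing 50:49 is not itself a defect.** A reader might infer that the trial fails whenever that split is not met. The documents do not support this: 50 and 49 are planning figures, and a fixed 6:5 split also usually misses them. Only large imbalance matters.

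**Simple randomisation is valid.** A reader might also infer that chance imbalance between so few groups confounds or biases the comparison. It does not. Under a proper random draw it adds variance. Education is already a planned covariate, so that imbalance is partly dealt with. Baseline PECC is not clearly a covariate. Adjustment also cannot restore the information lost to an 8:3 or 9:2 split.

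**Conclusion.** The point holds as a matter of efficiency and balance. As worded, the allocation method does not secure the equal arms on which the sample size rests. On an independent 1:1 draw per group, 6:5 arises 45% of the time, and the expected efficiency is about 92% of a 6:5 split. The chance of 8:3 or worse is 23%, which costs about eight points of power or more relative to 6:5.

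The split probabilities depend only on how simple allocation is read. The headcount figures also assume the spread of group sizes, and the power figures assume an SD and an ICC that the article does not give. If a 6:5 split was in fact preset, the point narrows to uneven headcount and uncontrolled baseline PECC.

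**What to change.** In the Randomisation section, replace simple allocation with the following:

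1. Fix the split at six groups against five, and draw at random which arm receives six.
2. After the baseline assessment, list the 462 possible splits. Keep those balanced on total participants and mean baseline PECC within limits set in advance, and draw one at random.
3. In the Data analysis section, state that the model adjusts for baseline PECC at participant level.

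Fixing 6:5 alone is not enough, because group sizes must enter the constraint for headcounts to come close. Reconcile the wording in the design section by stating the number of groups per arm.

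The cost is a short script, run once by the independent staff who already carry out the allocation, and slightly more analysis work. The limits must not be so tight that too few splits remain for a real random draw, so the number retained should be reported.

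If allocation has already taken place, report how it was drawn, give the groups and participants achieved in each arm, and adjust for baseline PECC.
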